#### Primary Analysis

The primary outcome variable defined is a change in the slope of eGFR in participants enrolled in the study compared to that of a matched cohort. Matching variables will include sex, race, time from transplant, living or deceased donor, and baseline eGFR.

eGFR will be summarized using descriptive statistics by study visit. Plots will be used as a general guideline to assess the functional relationship of eGFR over time for modeling purposes. Change in eGFR across time will be modeled using a linear mixed-effects (random intercept random slope) model.

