#### Secondary Analysis

Secondary outcomes include continuous outcomes, categorical outcomes, and time-to-event outcomes. Categorical outcomes will be evaluated using a chi-square test or the Fisher exact test, when appropriate. Death-censored graft loss will be evaluated using a Cox cause-specific hazards model. A cumulative incidence curve will be used as with 95% CIs using the cumulative incidence function. Graft and patient survival will be estimated using the Kaplan-Meier method. Factors associated with the risk of graft loss and patient death will be evaluated using a Cox extended hazards model. The effect of TruGraf test results and TRAC test results on the risk of graft loss and patient death will be incorporated in the model as time-varying covariates. Patient-reported outcome measures will be assessed using scoring tools from the Patient-Reported Outcomes Measurement Information System (PROMIS) group. Cut point methods will be used descriptively for each time point based on thresholds known by the PROMIS group at that time or linkages to legacy measures, when appropriate. Comparison across time points will be carried out using Meaningful Change Methods for each PROMIS measure based on information and guidance from the PROMIS group.

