**11A. How troublesome is it?**
Not at allVery littleModerately troublingVery troublingExtremely troubling

**Table 1 table1:** Schedule of assessments.

Enrollment or months post enrollment			Baseline visit (days –90 to 0)		3		6		9		12		15		18		21		24		27		30		33		36		Unscheduled visit		At workup for referral to transplant center
Visits	Details																														
Informed consent	Prior to any study-related procedures	✓																													
Assessment inclusion or exclusion criteria			✓																												
Participant’s demographics	Date of birth, sex, race, height, weight, and date of transplant	✓																													
Transplant information	Donor type and cause for renal failure	✓																													
Chemistry panel	Serum creatinine	✓		SOC^a^		SOC		SOC		SOC		SOC		SOC		SOC		SOC		SOC		SOC		SOC		SOC		SOC		SOC	
Immunosuppression medications	Name and changes in dose or medication			✓		✓		✓		✓		✓		✓		✓		✓		✓		✓		✓		✓		✓		✓	
Assessment of clinical events	Rejections, infections, graft Loss, and death	✓		✓		✓		✓		✓		✓		✓		✓		✓		✓		✓		✓		✓		✓		✓	
OmniGraf results	TruGraf and TRAC test results (if SOC laboratory tests are performed)	✓ (day 0)		✓		✓		✓		✓		✓		✓		✓		✓		✓		✓		✓		✓		✓		✓	
Patient’s medication-related symptom burden			✓		✓		✓		✓		✓		✓		✓		✓		✓		✓		✓		✓		✓		✓		✓
Biopsy information	Surveillance and for-cause: in case of rejection, type and grade			SOC		SOC		SOC		SOC		SOC		SOC		SOC		SOC		SOC		SOC		SOC		SOC		SOC		SOC	
Patient-reported outcomes	PROMIS^b^-29, PROMIS Self-Efficacy, and PROMIS Depression Scale	✓								✓								✓								✓					
Provider satisfaction			✓								✓								✓								✓				

^a^SOC: standard of care.

^b^PROMIS: Patient-Reported Outcomes Measurement Information System.

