### Study Endpoint Definitions and Assessment Plan

The following will be used to define and assess events within this study.

The primary endpoint is a comparison of the slope change in eGFR from baseline to the end of follow-up between the study participants and a matched control group. eGFR will be calculated using the 4-variable Modification of Diet in Renal Disease equation [16], with a sensitivity analysis performed using the Chronic Kidney Disease Epidemiology Collaboration equation [17]. Routine serum creatinine concentrations, which are measured as a part of usual care, will be utilized to estimate the GFR at baseline and at months 12, 24, and 36 post enrollment for assessments. The slope in eGFR change will be calculated for the entire follow-up for the primary outcome, with subanalyses performed between the other described time points. The matched control group will be a propensity-matched cohort from the US Medicare database.

Furthermore, we will compare the PROMIS Self-Efficacy for Managing Chronic Conditions–Managing Medications and Treatment–Short Form 4a scores at the end of follow-up relative to baseline [18]. This will measure changes in self-efficacy within the participant population—the belief that one can carry out a behavior necessary to reach a desired goal, even when a situation contained unpredictable and stressful elements. The study coordinator will provide access to the survey at baseline and at months 12, 24, and 36 post enrollment. Subanalyses will be performed among all time points.

We will then compare the PROMIS-29 Profile (version 2.1) scores at the end of follow-up relative to baseline [19]. This will measure changes in overall quality of life and satisfaction. The study coordinator will provide access to the survey at baseline and at months 12, 24, and 36 post enrollment. Subanalyses will be performed among all time points.

This will be followed by a comparison of the PROMIS Depression Scale scores at the end of follow-up relative to baseline [20]. This will measure changes in symptoms of depression. The study coordinator will provide access to the survey at baseline and at months 12, 24, and 36 post enrollment. Subanalyses will be performed among all time points.

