Hospitalizations, subcategorized for hospitalizations resulting from infections, will be compared between study participants and a matched control group. Study coordinators will obtain information on hospitalizations and causes at all follow-up events. This will be compared to hospitalizations and causes documented within the US Medicare database for a propensity-matched control group. Hospitalizations will be defined as admission to hospital with at least one overnight stay. Length of hospital stay will also be recorded.

MRSB, as defined as the change in the number and severity of ADE self-reported by study participants, will be recorded from the end of follow-up relative to baseline.

Overall graft failure, defined as return to chronic dialysis, transplant nephrectomy, retransplantation, or death, will also be recorded. The study coordinator capturing clinical event data will review the medical record at intervals in accordance with the schedule of evaluations to determine if a study participant has developed graft failure. The timing and cause of each graft loss will be recorded for comparative analysis with the propensity-matched external cohort. Patient death will be captured in a similar manner, with timing and cause recorded as well.

The anticipated first enrollment of participants in the study is October 2022, with data analysis and publication expected in October 2027.

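### Hospitalizations come from study coordinators for every participant and from Medicare records for every control, so a difference in capture or cause classification cannot be told apart from an OmniGraf effect.

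*Protocol article*

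**What the plan says.** All the relevant text is in the protocol article.

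- **Comparison intended** (Study Endpoint Definitions and Assessment Plan): "Hospitalizations, subcategorized for hospitalizations resulting from infections, will be compared between study participants and a matched control group".
- **Source for participants** (same section): "Study coordinators will obtain information on hospitalizations and causes at all follow-up events".
- **Source for controls** (same section): "This will be compared to hospitalizations and causes documented within the US Medicare database for a propensity-matched control group". The control group is external: "The matched control group will be a propensity-matched cohort from the US Medicare database".
- **Event definition** (same section): "Hospitalizations will be defined as admission to hospital with at least one overnight stay".
- **Matching** (Primary Analysis): "Matching variables will include sex, race, time from transplant, living or deceased donor, and baseline eGFR".
- **Test for categorical secondary outcomes** (Secondary Analysis): "Categorical outcomes will be evaluated using a chi-square test or the Fisher exact test, when appropriate".

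The article does not describe linking participants to Medicare, checking one source against the other, or a sensitivity analysis for unequal capture.

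**The concern.** A between-group contrast is interpretable only if the outcome is measured in the same way in both groups, or if the difference in measurement is known and corrected. Here every participant is measured by one system and every control by the other. No participant has Medicare capture and no control has coordinator capture, so the planned data hold nothing from which the effect of source could be estimated.

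Two things can differ between the sources. One is completeness, meaning the share of true admissions that reaches the dataset. The other is cause: an admission may be labelled infection-related from what a coordinator obtains in one group and from what the database documents in the other. The infection subcategory is exposed to both.

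What is at stake is a named secondary comparison. The abstract lists hospitalizations and their causes among the outcomes compared with the matched cohort. The Introduction and the section on resources and biomarker testing both cite fewer hospitalizations with a similar mobile health tool. Readers will take a difference as an effect. This is a stated design choice, and correct handling of censoring or exposure time in the analysis would not remove it.

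**Working it through.** The article gives no hospitalization rate, effect size or power for this outcome, so there is no planned figure to reproduce. The check has two parts.

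**1. Does anything in the plan equalize the two sources?**

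- Matching on sex, race, time from transplant, donor type and baseline eGFR balances patients. It cannot balance how admissions are found, because source does not vary within a group.
- The overnight-stay rule aligns what counts as an admission. It does not align how completely admissions are detected or how their cause is classified.
- No linkage or validation step is described.

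Source and group therefore remain fully confounded.

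**2. How large could the distortion be?**

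Assumptions, none of them given in the article:

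- true risk of at least one hospitalization is 50% in both groups, so there is no effect;
- admissions follow a Poisson process;
- coordinators capture c times the admissions that the Medicare source would show;
- the outcome is the proportion with at least one admission, tested at two-sided 5% with equal groups.

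Two group sizes bracket the range. One is 2000, the full enrolment matched 1:1. The other is 2000 × 0.5 × 0.5 = 500, which applies the article's dropout and missing-data allowances in turn.

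Formulas:

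- underlying rate λ = −ln(1 − 0.5) = 0.693
- observed control proportion p₁ = 0.50
- observed participant proportion p₂ = 1 − exp(−cλ)
- observed rate ratio under no effect = c
- probability of rejection from the two-proportion z-test, with standard error √[2p̄(1 − p̄)/n] under the null

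Worked case, c = 0.90: p₂ = 1 − exp(−0.90 × 0.693) = 0.464, a difference of −0.036. The null standard error is about 0.0316 at n = 500 and 0.0158 at n = 2000, so the expected z is about −1.14 and −2.27. The rejection probabilities are about 21% and 62%.

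| c | p₂ | false significance, n = 500 | n = 2000 | apparent direction |
|---|---|---|---|---|
| 0.70 | 38% | 96% | about 100% | favours OmniGraf |
| 0.85 | 45% | 41% | 94% | favours OmniGraf |
| 0.90 | 46% | 21% | 62% | favours OmniGraf |
| 0.95 | 48% | 9% | 20% | favours OmniGraf |
| 1.00 | 50% | 5% | 5% | none |
| 1.10 | 53% | 19% | 56% | against OmniGraf |

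A second model gives a similar picture. Let 40% of each group be truly hospitalized, with Medicare identifying 95% of those patients and coordinators 85%. The observed proportions are 0.40 × 0.85 = 0.34 and 0.40 × 0.95 = 0.38, an apparent risk ratio of 0.89. False significance is then 26% at 500 per group and 75% at 2000. In both models a larger sample makes the error more likely.

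**The case against.** The strongest reply is that the article does not show coordinators to be worse than Medicare. Clinical events are assessed every 3 months to month 36 and at unscheduled visits, and hospitalizations are to be obtained each time. Such active follow-up could find more than a payer file does. This stands. A reader might infer that the design tilts the result towards OmniGraf, but the document says nothing about the completeness of either source, so the bias may run either way.

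Other stronger readings also lack support:

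- **No prompt in the schedule.** The clinical-events row of Table 1 reads "Rejections, infections, graft Loss, and death" and does not name hospitalizations. The text nevertheless instructs their collection, and a condensed table label in an article is not evidence of missed admissions.
- **Unblinded judgement of cause.** The article says coordinators obtain causes. It does not say they adjudicate them.
- **Length of stay.** It is to be recorded, but no between-group comparison of it is specified.

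It is also fair to say that the common overnight-stay definition helps, that the capture values above are hypothetical, that the most extreme percentages need 2000 per group or a large capture gap, and that this is one of many secondary outcomes. The primary eGFR comparison does not depend on it. None of this restores comparability: uncertainty about direction means that a difference, or the absence of one, cannot be interpreted.

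**Conclusion.** The point holds as a measurement problem of unknown size and direction. The article states both sources and the direct comparison between them, and nothing in it separates source from group. The all-cause and infection-related hospitalization comparisons, as planned, cannot attribute a difference to OmniGraf.

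Under the 50% risk assumed above, a 10% relative difference in capture raises the false-significance rate from 5% to roughly 20% with 500 per group and roughly 55% to 60% with 2000, in whichever direction capture differs. These figures show sensitivity and do not predict the bias in this study. Because the outcome is secondary, the change should be made, but the primary conclusion is not at risk from it.

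**What to change.** 1. Make the between-group hospitalization comparison on one source. For participants with Medicare coverage who can be linked, take admissions and infection category from the Medicare records, using the same inpatient-stay and infection-cause algorithm as for controls. Compare them with their own matched controls.
2. Keep coordinator-reported admissions for all participants as a descriptive, participant-only outcome.
3. Use the linked participants to check coordinator capture and cause against Medicare, and report the agreement.
4. Before enrolment, confirm that the consent and HIPAA authorization cover linkage, or extend them. The Inclusion Criteria require an authorization but do not say that it reaches Medicare records. The article describes ethics review as under way and first enrolment as anticipated, so the wording may still be open to change.
5. If linkage proves impossible, present the cross-source comparison as descriptive, with a prespecified bias analysis that varies relative capture below and above 1.

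The cost is linkage identifiers, consent wording, and the addition of participants to an extract already needed for controls. The main downside is that the comparison is limited to linkable, Medicare-covered participants. Medicare coverage is not an eligibility requirement, and the article does not give the size of that subset, so precision could fall and the result would apply to that subset only.

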### Statistical Analysis

#### Sample Size Requirements

Sample size was determined using an SAS macro program, %GFR_Slope_Power, developed by Vonesh et al [14] specifically for the purpose of determining sample size or power estimates for comparing slopes between 2 treatment groups based on the linear spline mixed-effects model. An Assumption of eGFR slope change over 3 years in standard care was adopted in accordance with Vincenti et al [15]. Collectively, it is estimated that a sample of 450 patients per protocol would be required to detect a minimum total slope difference at 1.08 mL/minute/1.73 m^2^/year with 84% power, assuring that the study will be powered for a clinically meaningful difference of 5 mL/minute/1.73 m^2^/year. Conservatively assuming a 50% dropout rate and 50% loss to follow-up or missing data for end of follow-up, for this analysis, a sample size of 2000 participants should be sufficient to demonstrate a clinically significant difference in the primary outcome. Annual and as-needed review by an advisory board will halt enrollment when it is predicted that the sample size will be met.

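### Participants' graft failures and deaths come from scheduled record review while the controls come from Medicare, so events after a participant leaves may be missed in one group only

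*Protocol article*

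**What the plan says.** The section Study Endpoint Definitions and Assessment Plan fixes both the event and how it is found. "Overall graft failure, defined as return to chronic dialysis, transplant nephrectomy, retransplantation, or death, will also be recorded." The coordinator who captures clinical events "will review the medical record at intervals in accordance with the schedule of evaluations to determine if a study participant has developed graft failure". For deaths: "Patient death will be captured in a similar manner, with timing and cause recorded as well." No other source is named for participants.

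The same section sets the comparison: "The timing and cause of each graft loss will be recorded for comparative analysis with the propensity-matched external cohort." It also names the source of the controls: "The matched control group will be a propensity-matched cohort from the US Medicare database."

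Under Sample Size Requirements the plan allows for heavy attrition: "Conservatively assuming a 50% dropout rate and 50% loss to follow-up or missing data for end of follow-up". In Table 1, the row for clinical events, which includes graft loss and death, is ticked at every quarterly visit, at unscheduled visits and in the column headed "At workup for referral to transplant center".

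Under Secondary Analysis, categorical outcomes get a chi-square or Fisher test, and graft and patient survival get Kaplan-Meier and Cox methods. The listed secondary outcomes include the proportion with graft survival at year 3 after transplantation, and graft loss or death over the three study years.

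**The concern.** The two groups have different event sources. A participant's dialysis, retransplantation or death is known if it reaches the record that the coordinator reviews. A control's event is known if it reaches a payer database, which does not depend on anyone attending a study visit. If participants leave and nothing else follows them, their later events can be lost while comparable events in controls are still counted.

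Lost events in one group make that group look better, and here it is the OmniGraf group. The suggested framework uses OmniGraf results when weighing changes to immunosuppression, and the Introduction itself names the rejection risk of such changes. Graft loss and death are the outcomes in which harm from those changes would appear, so an error towards benefit matters even though they are secondary.

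A later analysis plan could not easily repair this. Events that were never collected cannot be recovered in analysis, and linkage needs identifiers and authorization obtained at consent.

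**Working it through.** **1. The plan's own attrition figure.** The section states that "a sample of 450 patients per protocol would be required to detect a minimum total slope difference at 1.08" mL/minute/1.73 m² per year. Compounding the two allowances gives 450 / (0.5 × 0.5) = 1800. In the other direction, 2000 × 0.25 = 500, which covers 450. So 2000 is consistent with 1800 rounded up. The allowance means 1000 of 2000 remaining after dropout alone, and 500 with end-of-follow-up data if both losses apply.

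**2. Inputs for the illustration.** From the plan: 2000 participants, three years of follow-up, and leaving L = 50% (dropout alone) or 75% (both allowances read as leaving, an upper case). Assumed, because the article gives no figures: true three-year failure F = 12% in both groups, constant hazards, 2000 controls, all events after leaving missed in participants and none missed in controls.

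**3. Crude proportion, leavers kept as event-free.**
- Failure hazard h = −ln(0.88)/3 = 0.0426 per year.
- Leaving hazard c = −ln(0.5)/3 = 0.2310 per year.
- Observed failure = h/(h+c) × [1 − exp(−3(h+c))] = 0.0426/0.2737 × (1 − 0.88 × 0.5) = 8.7%, against a true 12%.
- About 73% of events are captured: 174 against 240 per 2000.
- With L = 75%, c = 0.4621 and observed failure is 0.0426/0.5047 × (1 − 0.88 × 0.25) = 6.6%. About 55% are captured: 132 against 240.

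This arises even if leaving has nothing to do with failure. For graft survival at year 3 *after transplantation* the loss would be smaller. Participants enrol 3 months to 2 years after transplantation, so they reach that point 1 to 2.75 years after enrolment, when fewer have left.

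**4. Kaplan-Meier or Cox, censoring at leaving.** Let the hazard be h₀ before leaving and r·h₀ after. Solve for h₀ so that overall true failure stays at 12%:

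exp(−3(h₀+c)) + ∫₀³ c·exp(−(h₀+c)t)·exp(−r·h₀(3−t)) dt = 0.88.

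Participants then show 1 − exp(−3h₀), and the spurious hazard ratio is about 3h₀ / 0.1278, where 0.1278 = −ln(0.88).

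| r | h₀ (L = 50%) | Participants' Kaplan-Meier failure (L = 50%) | Hazard ratio (L = 50%) | Hazard ratio (L = 75%) |
|---|---|---|---|---|
| 1 (leaving unrelated) | 0.0426 | 12.0% | 1.00 | 1.00 |
| 1.5 | 0.0375 | 10.6% | 0.88 | 0.81 |
| 2 | 0.0335 | 9.6% | 0.79 | 0.69 |
| 3 | 0.0277 | 8.0% | 0.65 | 0.53 |

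The size therefore turns on r, the link between leaving and failure, for which the article gives no value. With true failure of 10%, 15% or 20% the ratios are almost the same (0.88 to 0.65–0.66 at L = 50%).

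**The case against.** Four readings go further than the documents allow.

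- **That half or more will leave.** The 50% figures are a conservative planning allowance for the eGFR slope analysis, not a forecast. The second includes missing data. Laboratory tests are not mandated, so someone without a month-36 creatinine may still have a record showing dialysis or death.
- **That the referral column in Table 1 shows where patients are lost.** It is a capture point: clinical events are ticked there. Nothing says follow-up ends at referral.
- **That capture is confined to the site's own chart and is complete in the controls.** The article speaks only of the medical record. It does not say how completely graft failure and death are found in the Medicare cohort, or when controls are censored.
- **That if a share q of participants' events is missed, the hazard ratio is 1 − q.** This holds only if leavers stay at risk as event-free. Censoring at leaving removes their person-time too. At L = 50% with leaving unrelated to failure, q is 27%, yet the hazard ratio is 1.00, not 0.73.

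It is also fair to say that a condensed article may leave follow-up after withdrawal, linkage and censoring dates to the full protocol. That lowers certainty about what will happen in practice. It does not remove the point, because the article does state how events are found, names one route for participants, and compares the result with a different kind of source.

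**Conclusion.** The concern holds in a conditional form. As written, the groups have different event sources, the plan allows for heavy attrition, and no source is named for participants' events after leaving. Events may therefore be missed in participants only.

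Crude proportions are biased directly if leavers are counted as event-free. Kaplan-Meier and Cox estimates are biased only if leaving is related to failure: from no bias at all to a spurious hazard ratio of about 0.65 at 50% leaving, over the range of r examined. The 12% risk, the constant hazards, r, and complete capture in controls are all assumptions. Under them the direction favours OmniGraf. A reader might infer that the survival results *are* biased towards OmniGraf, but the documents do not support that flat statement, because r and the completeness of control capture are unknown. The point concerns secondary outcomes and does not touch the eGFR slope.

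**What to change.** For the between-group comparison of graft and patient survival, take dialysis return, retransplantation and death from the same Medicare source in both groups, with the same coverage rule and closing date. Include every consented participant who can be linked, including those who stop testing or leave the site. State whether transplant nephrectomy, which is part of the definition, is taken from that source for both groups or left out of the comparison for both. Use the chart to add cause of graft loss and death in participants.

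Report chart-ascertained results for all participants descriptively and as a sensitivity analysis. In any chart-based analysis, state when leavers are censored, and do not count them as event-free in year-3 proportions.

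The cost is linkage wording and identifiers at consent, one further data extract, and a smaller comparison. Eligibility does not require Medicare coverage, so some participants cannot be linked, and those who can may differ from the rest; the number linked and their characteristics should be reported. No extra visits or patients are needed. The article describes ethics review as still under way when it was written, and the consent wording is cheapest to change at that stage.
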